**Methods::**

This study is a randomized, double-blinded, placebo-controlled, single-central clinical trial. A total of 140 participants are randomly allocated to 2 groups: the intervention group and the placebo group. Based on routine medications, the intervention group will be treated with YLS and the placebo group will be treated with YLS placebo. All participants will receive a 8-week treatment and then be followed up for another 12 months. The primary outcome measures are N terminal pro B type natriuretic peptide (NT-proBNP) and left ventricular ejection fraction. Secondary outcomes are plasma levels of microRNA-145, plasma cardiac enzyme, and Troponin I levels in blood samples, changes in ST-segment in ECG, Seattle Angina Questionnaire, the efficacy of angina symptoms, and occurrence of major adverse cardiac events. All the data will be recorded in case report forms and analyzed by SPSS V.17.0.

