Chinese herbal medicine (CHM), especially combined herbal formulations, has been widely used in traditional Chinese medicine for the treatment of myocardial infarction for hundreds of years and has attracted increasing attention in drug research.^[10]^ In the theory of Traditional Chinese Medicine (TCM), the collocation of monarch herbs and minister herbs is assembled according to the pathogenesis of patients with further prescription to adapt to the different pathogenesis of MIR. In the diagnosis of MIR, “blood stasis and heat syndrome” is an important syndrome based on the viewpoint of TCM theory and our previous clinical practice.^[11]^ TCM practitioners attach importance to preventing disease before it arises and controlling the development of existing disease. And, there are some special advantages for TCM in ameliorating myocardial ischemia-reperfusion injury.^[10]^

Yiqi Liangxue Shengji prescription (YLS) is a based on the TCM theory of “invigorating qi, activating blood and clearing up the heat of blood” for the prevention of MIR in China. Clinical trials have shown that YLS is effective in improving clinical symptoms and ameliorating the major adverse cardiovascular events (MACE) of coronary heart disease patients undergoing percutaneous coronary intervention.^[12,13]^ YLS consists of 4 herbal medicines (Table 1), including Astragalus membranaceus (Huang Qi), Salvia miltiorrhiza (Dan Shen), Cortex Moutan (Mudan Pi), Lonicerae japonicae flos (Jinyin Hua). Among them, Radix Astragali and Salviae Miltiorrhizae are the principal pharmacologically active components. They exhibit superior anticardiac reperfusion injury action in animals, including restoring cardiac mechanisms, such as coronary blood flow, lipid peroxide content, superoxide dismutase activity, the release of inflammatory mediators, and so forth, to favorable levels after reperfusion.^[14,15]^ However, there is no clinical evidence for YLS in the treatment of MIR. Therefore, we designed a randomized, double-blinded, placebo-controlled, single-central clinical trial aiming to evaluate cardiac protection from Yiqi Liangxue Shengji prescription in patients with AMI after PCI.

**Table 1 T1:** Components and dose of Yiqi Liangxue Shengji prescription.

Chinese name	English name	Pharmacological effects	Main active components	Weight (g/bag)	Reference

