### Removal, dropout, and termination criteria

2.5

Participants can voluntarily drop out at any time during the trial. Eligible subjects failing to complete the observation period presented in the trial will be considered as dropout cases regardless of the time and reason. Reasons for dropout will be recorded, and the last data recorded for these participants will be included in the data analysis. The trial will be suspended in a specific participant if serious adverse events (AEs) relevant to the YLS occur; the participant decides to join in another clinical research project in terms of cardiovascular diseases; the participant demonstrates hypersensitivity toward YLS, such as abnormal thirsty, stomach ache, and diarrhoea; the participant suffers from acute life-threatening disease. The whole research would be terminated in the following circumstances: masking of the randomization fails; unblinding rate exceeds 20% of the sample size; assessments of all follow-up are completed.

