#### Primary and secondary outcomes

2.8.3

The primary outcome measures of the study are NT-proBNP and left ventricular ejection fraction, which will be measured at baseline and 8 weeks after randomization. Secondary outcomes include plasma levels of microRNA-145, plasma creatine kinase-MB, and CardiaC Troponin I levels in blood samples. At the same time, the trial also observes the occurrence of MACEs defined as the composites of deaths from any cardiac causes, myocardial infarction, and revascularization (PCI or CABG) at 8 weeks after randomization. The efficacy of angina symptoms, Seattle Angina Questionnaire, will be recorded at baseline and 8 weeks after randomization and TCM syndrome efficacy.^[24]^ Items to be measured and the time window of data collection are shown in Table 3.

**Table 3 T3:** Schedule of data collection.

Items	Screening period within 1 wk	Treatment period 4–8 wk	Follow-up period 2–12 mo
Signed informed consent	√		
Inclusion/exclusion criteria	√		
Demographic data	√		
Medical history, course of disease, treatment history	√		
Combined diseases	√		
Concomitant medications	√	√	
LVEF	√	√	
NT-proBNP	√	√	
microRNA-145	√		
CK-MB	√		
cTnI	√		
MACEs			√
SAQ	√	√	
TCM syndrome efficacy	√	√	
Vital signs	√	√	
Blood, urine and stool routine	√	√	
Liver and kidney function	√	√	
Adverse events		√	√

Vital signs: temperature, heart rates, breathing, and blood pressure.

CK-MB = creatine kinase-MB, cTnI = CardiaC Troponin I, LVEF = left ventricular ejection fraction, MACE = major adverse cardiac event, SAQ = Seattle Angina Questionnaire, TCM = Traditional Chinese Medicine.

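### A death before week 8 would normally enter both primary analyses as no change, and no listed outcome counts deaths from all causes

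*Protocol article*

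**What the plan says.** Section 2.8.3 fixes the primary outcomes and their timing: "The primary outcome measures of the study are NT-proBNP and left ventricular ejection fraction, which will be measured at baseline and 8 weeks after randomization".

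Section 2.5 fixes what happens to people who do not reach week 8: "Eligible subjects failing to complete the observation period presented in the trial will be considered as dropout cases regardless of the time and reason". Their reasons are recorded, and "the last data recorded for these participants will be included in the data analysis". Death is not mentioned as an exception.

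The only listed efficacy outcome with a death component is MACE, defined in section 2.8.3 as "deaths from any cardiac causes, myocardial infarction, and revascularization (PCI or CABG) at 8 weeks after randomization". The other secondary outcomes there are biomarkers ("Secondary outcomes include plasma levels of microRNA-145, plasma creatine kinase-MB, and CardiaC Troponin I levels in blood samples"), angina measures and TCM syndrome efficacy. The abstract's list ends with "changes in ST-segment in ECG, Seattle Angina Questionnaire, the efficacy of angina symptoms, and occurrence of major adverse cardiac events" and has no mortality outcome either. Section 2.8.2 builds safety on vital signs, laboratory tests and adverse events, and does not name death.

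**The concern.** A dead participant has no week-8 NT-proBNP or LVEF. The plan nevertheless supplies a value, because section 2.5 applies the last recorded data to every non-completer. That value was measured while the person was alive, and it normally predates any treatment effect. The worst result a participant can have is then analysed as a neutral one. This applies to deaths of any cause, cardiac deaths included, and to both primary outcomes.

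MACE only partly makes up for this. A cardiac death is counted there. A fatal bleed or a fatal stroke is not counted as such in any listed efficacy outcome. The article gives some reason to care about such deaths: Table 1 lists anticoagulant and antithrombotic effects for one of the herbs, and section 2.6 gives the study product alongside dual antiplatelet therapy. If deaths differed between arms, the efficacy tables would understate the difference, and a reader would have to rebuild it from adverse-event listings.

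**Working it through.** **The rules side by side**

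1. Planned primary measurements: baseline and week 8 (section 2.8.3).
2. Participant dies between them: a non-completer, so a dropout under section 2.5.
3. Last recorded data: normally the baseline value, so the change from baseline is 0.
4. Comparison: section 2.4 excludes an ejection fraction below 35%. A participant enrolled at 35% who dies is carried at 35%, change 0. A survivor who goes from 35% to 30% has a change of −5 points. The survivor scores worse.

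Section 2.10 mentions an echocardiogram at 1 month, and Table 3 labels the treatment column as 4–8 weeks. If an interim value exists, a later death would carry that value instead. It is still a value from a living participant, so the problem remains.

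**How many deaths this touches**

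The plan gives no expected number of deaths, so there is no figure of its own to reproduce. Inputs:

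- N = 140 (section 2.7).
- One-year mortality of 7% after primary PCI (Introduction).
- Timing of deaths within the year: not given. Two cases are assumed, constant hazard and half of the deaths before week 8.
- Non-cardiac share: not given. Assumed to be 10–30%.

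Deaths over one year: 140 × 0.07 = 9.8.

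Constant hazard:
- Risk by week 8 = 1 − (1 − 0.07)^(8/52) = 0.0111.
- Deaths by week 8 = 140 × 0.0111 = 1.6.
- Chance of at least one = 1 − 0.93^(140 × 8/52) = 1 − 0.93^21.54 = 0.79.

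Half early:
- Deaths by week 8 = 140 × 0.035 = 4.9.

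| Timing | Deaths by week 8, any cause | Non-cardiac at 10% | Non-cardiac at 30% |
|---|---|---|---|
| Constant hazard | 1.6 | 0.16 | 0.47 |
| Half early | 4.9 | 0.49 | 1.47 |

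The second column is the number given a carried-forward primary value. The last two columns are the number that MACE at 8 weeks would not count. With 70 per arm, each carried-forward death is 1/70 = 1.4% of its arm.

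**The case against.** The strongest reply is that most of this is a legitimate choice. A cardiac-death composite is a recognised definition, MACE is only secondary, and the abstract and the Table 3 footnote both expand the term as cardiac. The Introduction's reference to "ameliorating the major adverse cardiovascular events (MACE) of coronary heart disease patients" concerns previous trials and does not define this trial's outcome. Adverse events are scheduled through treatment and follow-up, so deaths are not lost to safety reporting. The article also concedes that it lacks clinical endpoints and has a small sample. All of this stands, and it is why the cardiac composite need not be replaced.

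Four stronger readings are tempting, and the document does not support them.

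- **Non-cardiac deaths are scored as MACE-free.** The article does not say so. Section 2.11 uses at-risk and censoring language for patients lost to follow-up, so in a time-to-event analysis such a death might be censored. Either way it is not an event, but it is not shown to be a success.
- **Unexplained deaths are left out of MACE.** The article does not say how they are classified, and they could be counted as cardiac. The detail of cause-of-death review may lie in a fuller document.
- **One to three deaths go uncounted.** This takes 10–30% of the 9.8 deaths at one year (1.0–2.9). It does not fit an 8-week endpoint unless nearly all deaths of the year fall in those weeks.
- **The uncounted deaths could change the result.** Suppose 4 counted events per arm and 2 uncounted deaths, both on YLS. The risk ratio goes from 1.0 to (6/70)/(4/70) = 1.5, with an approximate 95% interval of 0.44 to 5.1. Neither version supports a conclusion, and placing both deaths in one arm is a construction.

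It can also be said that last-value carry-forward is a wider problem than death. That is true, but for other dropouts a week-8 value exists in principle and is missing. For the dead it does not exist, so a separate rule is needed.

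**Conclusion.** The point holds for what the article itself fixes. The dropout rule in section 2.5, read with the measurement times in section 2.8.3, would normally analyse a death before week 8 as no change on both primary outcomes. No listed outcome counts deaths from all causes.

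The size is modest: about 1.6 deaths before week 8 at constant hazard and 4.9 if half fall early, of which about 0.2–0.5 and 0.5–1.5 respectively would be non-cardiac. This rests on the cited 7% applying here, on the two assumed timings and on the assumed 10–30% share. The exclusions for low ejection fraction, severe arrhythmia, renal insufficiency, malignancy and bleeding risk may make 7% too high for this population, while clustering of deaths soon after infarction would push towards the larger figures.

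The primary-outcome part carries the more weight, because there a stated rule assigns the wrong value. Nothing here shows that the cardiac MACE definition is an error or that a conclusion of the trial would be reversed.

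**What to change.** - **Section 2.5:** exempt deaths from the last-data rule, and record death separately from other reasons for not completing.
- **Section 2.8.3, primary outcomes:** add one pre-specified supplementary analysis each for NT-proBNP and LVEF, in which a death before week 8 ranks below every survivor.
- **Section 2.8.3, MACE:** keep the cardiac composite if preferred, and report all-cause death by arm beside it.

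The cost is wording plus one rank analysis per primary outcome, with no added participants or visits. Vital status does have to be sought for people who stop attending, since the article expects some loss to follow-up. A rank result is less directly interpretable than a mean difference, which is why it is proposed as supplementary.

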### Adverse events

2.9

AEs are defined as negative or unintended clinical manifestations following the treatment. Patients will be asked to report to the investigators any abnormal reactions occurring at any time during the trial. In addition, investigators will collect information about abnormal reactions monthly. All details of related and unexpected AEs, such as time of occurrence, degree and duration of AEs, suspected causes, and the effective measures and outcomes will be recorded on electronic case report form. Any AEs, such as subjective discomfort and laboratory abnormalities, should be taken seriously. Careful analysis and immediate measures are taken to protect the safety of the subjects until the adverse events disappeared.

### Quality control of data

2.10

Patients’ baseline characteristics are collected with case report forms (CRFs) during hospitalization at least 24 hours after PCI by investigators of each center. Angiographic data are recorded in the PCI procedure. According to the follow-up plan, patients are required to undergo recording of history and echocardiogram in each center at 1- and 12-month follow-up.

Data usage adheres to local laws and regulations of participating centers. Patient privacy is protected by restricting the access to dataset to relevant individuals—investigators, statistical analyzers, clinical research associates, and representatives of the ethics committee—and replacement of the actual names in the documents with serial numbers. Representatives of participating centers are responsible for collecting data of enrolled patients in that center and uploading to the database. Angiographic and echocardiographic data are stored in CD-ROMs and sent to a core lab in Dongfang Hospital, where the data are analyzed by specialists blinded to random allocation.

### Statistical analyses

2.11

The statistical analyses of primary and secondary outcomes will be conducted in both the intention-to-treat set and the per-protocol set. Primary and secondary endpoint data will be collected for the entire follow-up period for all patients. Patients lost to follow-up will be considered at risk until the date of last contact, at which point they will be censored. In the per-protocol set, patients who undergo randomization but withdraw consent to participate or not treated according to the allocated procedure after randomization will be excluded from per-protocol statistical analyses.

IBM SPSS V17.0 software pack was used for data analysis. The normal distribution of the data was tested with Pearson test. Independent sample *t* test was used for the comparison of data with normal distribution, while Spearman test was used for the comparison of data without normal distribution. Data with normal distribution were expressed as arithmetic mean ± standard deviation, while data without normal distribution were expressed as median value (minimum–maximum). A *P* value between .1 and .05 was considered marginally significant, a *P* value between .01 and .05 was considered significant, .001 and .01 highly significant, and < .001 very highly significant.

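### Section 2.11 censors patients lost to follow-up but names no comparison test that can use a censoring time, so its rule for MACE cannot be carried out as written

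*Protocol article*

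**What the plan says.** All references are to the protocol article.

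- **Scope (Section 2.11, Statistical analyses).** "The statistical analyses of primary and secondary outcomes will be conducted in both the intention-to-treat set and the per-protocol set".
- **Losses (Section 2.11).** "Patients lost to follow-up will be considered at risk until the date of last contact, at which point they will be censored". Endpoint data are to be collected over the whole follow-up period.
- **Tests (Section 2.11).** The independent-samples t "test was used for the comparison of data with normal distribution, while Spearman test was used for the comparison of data without normal distribution". Pearson is named only as a check of normality. No survival method, test of proportions or two-sample rank test is named.
- **Dropouts (Section 2.5).** Anyone who does not complete observation is a dropout, and the last data recorded for that patient enter the analysis.
- **MACE (Section 2.8.3).** The outcome is defined as "composites of deaths from any cardiac causes, myocardial infarction, and revascularization (PCI or CABG) at 8 weeks after randomization". The Abstract lists it among the secondary outcomes. Table 3 ticks it only in the follow-up column, 2 to 12 months, and not in the treatment period.

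**The concern.** Being at risk until a date and then censored has meaning only in a time-to-event analysis. NT-proBNP and LVEF are values measured at baseline and 8 weeks and have no time at risk, so the natural target of the rule is MACE. Yet the section offers no method that can apply it.

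An event outcome is not normally distributed. Taken at its word, the two-branch rule therefore sends MACE to Spearman. To run it, the analyst must code each patient as event or no event, and a patient lost early is then recorded as event-free to the end. That is what the censoring sentence rules out.

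MACE is the trial's hard clinical outcome, and the Discussion gives long-term benefit as part of the aim. At stake are a comparison that can drift if the arms lose patients at different rates, and a MACE result reported as a correlation and a P value, without a hazard ratio or risk difference and its interval.

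**Working it through.** **Step 1. Set the stated rules against the stated tests.**

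| Rule or test | Where | Can it use a censoring time? |
|---|---|---|
| At risk to last contact, then censored | 2.11 | Requires a method that can |
| t test (normal data) | 2.11 | No |
| Spearman (non-normal data) | 2.11 | No; it measures correlation |
| Last recorded data enter the analysis | 2.5 | No; for MACE it carries the last event-free status forward |

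The mismatch lies in the text itself and needs no arithmetic. The plan states no figure on this point to reproduce.

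**Step 2. Size of the bias if lost patients are coded event-free.** Assumptions, none from the protocol: the same true risk R in both arms, constant hazard, and losses uniform over the period. Let d be the proportion lost in an arm.

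- Hazard: h = −ln(1 − R). For R = 20% at 12 months, h = −ln(0.8) = 0.2231.
- Chance that the event comes before a uniform loss time: q = 1 − R/h = 1 − 0.2/0.2231 = 0.1037.
- Apparent risk: (1 − d)R + dq.

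| Lost, YLS v placebo | Apparent risk, YLS | Apparent risk, placebo | Ratio (true value 1) |
|---|---|---|---|
| 10% v 10% | 0.90 × 0.2 + 0.10 × 0.1037 = 19.0% | 19.0% | 1.00 |
| 12% v 8% | 0.88 × 0.2 + 0.12 × 0.1037 = 18.8% | 0.92 × 0.2 + 0.08 × 0.1037 = 19.2% | 0.98 |
| 20% v 5% | 0.80 × 0.2 + 0.20 × 0.1037 = 18.1% | 0.95 × 0.2 + 0.05 × 0.1037 = 19.5% | 0.93 |

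Section 2.7 plans for 10% dropout overall. With 70 per arm (140/2), the last row is a shift of 70 × (0.1952 − 0.1807) ≈ 1.0 event. The standard error of the log risk ratio with 14 events per arm is √(2/14 − 2/70) = 0.34, against a bias of ln(0.926) = −0.077.

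**Step 3. The same at 8 weeks.** With an assumed R = 5%, h = 0.0513 and q = 1 − 0.05/0.0513 = 0.0252. At 20% v 5% lost, the apparent risks are 4.50% and 4.88%, a shift of 70 × 0.0037 ≈ 0.26 events.

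**Step 4. Do the named tests fail on yes/no data in themselves?** Take 4 v 0 events with 70 per arm:

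| Test | P |
|---|---|
| t test | 0.0428 |
| Spearman on the group code | 0.0428 |
| Uncorrected chi-square | 0.0424 |
| Barnard's exact | 0.0485 |
| Fisher's exact | 0.1196 |

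On an illustrative four-level ordinal outcome with 63 per arm, Spearman gives 0.275 and Mann-Whitney 0.274. The tests do run. What they cannot take in is a censoring time, and Spearman does not return an effect on the risk or hazard scale.

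**The case against.** The strongest reply is that no sentence assigns a test to MACE. The two-branch rule is tied to normality and to mean ± SD or median with range, so it can be read as covering continuous data only. The MACE test is then merely unstated, which a condensed article may leave to an analysis plan. This stands in part: that MACE will be compared by Spearman is an inference. But the section opens by covering all primary and secondary outcomes and itself fixes a censoring rule. A further document could add a method; the published text would still hold a rule that its own tests cannot apply, and a dropout rule in Section 2.5 that conflicts with it.

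A second reply is that MACE at a fixed 8 weeks can properly be analysed as a proportion. That is true, but Table 3 ticks MACE only from 2 to 12 months and Section 2.11 collects endpoints over the whole follow-up, so the horizon is unsettled.

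Stronger readings are tempting and are not supported:

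- *The named tests cannot handle categorical data.* Step 4 shows that they run on 0/1 and ordinal data and agree closely with the usual tests.
- *A few events would earn false significance, as the gap from Fisher's test shows.* The gap mostly reflects Fisher's conservatism. At an assumed 5% risk with 70 per arm, its true error rate at .05 is 1.4%, and that of the t test is 4.8%.
- *The angina and TCM efficacy outcomes are graded and so are mishandled.* Section 2.8.3 gives no grading scale for either.
- *As written, the arm that loses more patients looks safer.* As written, those patients are censored. The distortion arises only if the named tests are applied in spite of that rule.

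**Conclusion.** The point holds in a limited form. Section 2.11 fixes a censoring rule and names only tests that cannot use it. It also names a correlation as the comparison for all non-normal data, and Section 2.5 gives a competing rule for dropouts. Applied literally to MACE, the named tests would treat lost patients as event-free and give no hazard ratio or risk difference.

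The numerical effect is modest. There is no bias in the risk ratio with equal losses, though both risks read slightly low. The ratio is 0.98 at 12% v 8% lost and 0.93 at 20% v 5%, the last being about one event per 70 patients and well inside sampling error. These figures rest on an assumed 20% 12-month risk, constant hazard and uniform losses. At 8 weeks with an assumed 5% risk, the shift is about a quarter of an event. MACE is secondary, the article already concedes that the sample is small and clinical endpoints are lacking, and the primary outcomes are outside this point. It should be corrected because the text contradicts itself and the repair is cheap, not because a large bias has been shown.

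**What to change.** Amend Sections 2.5, 2.8.3 and 2.11 and Table 3:

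1. Limit the t-test/non-normal rule to continuous or ordinal outcomes, and replace Spearman with the Wilcoxon rank-sum (Mann-Whitney) test.
2. Reconcile the MACE horizon (8 weeks in Section 2.8.3, 2 to 12 months in Table 3), and collect MACE from randomisation.
3. Name the method that fits the chosen horizon. Over the full follow-up: time from randomisation to first event in the intention-to-treat set, with Kaplan-Meier curves, a log-rank test and a Cox hazard ratio with 95% CI, censoring at last contact as already stated. Use a penalised estimate if an arm has no events, since the ordinary Cox estimate is then not finite. If fixed at 8 weeks: a risk difference with a score or exact 95% CI.
4. State that the last-recorded-data rule in Section 2.5 does not apply to MACE.

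The cost is a few sentences, one change to the collection schedule so that events in the treatment period are captured, and a little more analysis work. The censoring rule already requires last-contact dates; event dates must be recorded with them. MACE results may look less favourable than under the present wording.

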### Sample size calculation

2.7

The formula used to calculate the sample size is as follows, which is based on superiority clinical trial hypothesis test sample size estimation.^[23]^ The sample size was calculated on the basis of expected reduction in NT-proBNP. One previous study suggested that the reducing value for NT-proBNP level in AMI patient treatment with PCI is 32%. Therefore, we assume the reduction in NT-proBNP level as 58% in this study. Given a type I error rate of α = 0.05, type II error rate of β = 0.2, Uα(0.05)=1.65, Uβ (0.2) =1.28. The sample size for 1 arm needs to be 63, resulting in n = 2 × 63 = 126 patients. Considering a dropout rate of 10%, a total of 138 patients need to be allocated to reach the required number of patients for the efficacy analysis. For convenience of randomization, we decided to recruit 140 patients. The formula used to calculate the sample size is as follows:$$\text{n1}={\left(\text{U}\alpha +\text{U}\beta \right)}^{2}\times 2P\times (1-P)/{\left(P1-P2\right)}^{2}=\text{n2}$$

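### A loosely named normality pre-test chooses the test and effect measure for both primary outcomes, so the effect measure is not known in advance

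*Protocol article*

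**What the plan says.** Section 2.8.3 names two primaries: "The primary outcome measures of the study are NT-proBNP and left ventricular ejection fraction, which will be measured at baseline and 8 weeks after randomization". Section 2.11 gives one analysis rule for all outcomes: "The statistical analyses of primary and secondary outcomes will be conducted in both the intention-to-treat set and the per-protocol set".

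The rule has two steps. First, "The normal distribution of the data was tested with Pearson test". Then the branch follows from the answer. If an outcome passes: "Independent sample *t* test was used for the comparison of data with normal distribution". If it fails, the article turns to a different procedure: "Spearman test was used for the comparison of data without normal distribution". The descriptive statistics switch with the branch, from mean and standard deviation to median and range.

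The article does not say which Pearson procedure is meant or what threshold applies. Nor does it say whether raw values or changes are tested, or whether this is done by arm or pooled. No other section names a separate analysis for NT-proBNP or LVEF.

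**The concern.** There are two linked defects.

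- **The named test.** A Pearson test usually means a correlation or a chi-square test of association, and neither says anything about normality. The charitable reading is the chi-square goodness-of-fit test on binned data. That is a real normality test, but its result depends on the bins, and it often misses mild skew.
- **The selection step.** Even a good normality test would leave the primary effect measure to be decided by the observed data. A t test estimates a difference in means. A rank-based result answers a different question, and a Spearman coefficient gives no between-arm difference at all. LVEF could be reported one way and NT-proBNP the other, or one outcome could change measure between the intention-to-treat and per-protocol sets. Replacing Spearman with a proper two-sample rank test would not remove this step.

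At stake is whether a reader can know before the results what quantity each primary comparison estimates.

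**Working it through.** **Inputs from the article (section 2.7).** The assumed reductions are 32% and 58%, with "Given a type I error rate of α = 0.05, type II error rate of β = 0.2, Uα(0.05)=1.65, Uβ (0.2) =1.28". The article's own formula with P = (0.32 + 0.58)/2 = 0.45 gives

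(1.65 + 1.28)² × 2 × 0.45 × 0.55 / 0.26² = 8.585 × 0.495 / 0.0676 = 62.9, so 63 per arm.

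This reproduces the stated figure. It is used here only as the sample size for the checks. The mismatch between β = 0.2 and 1.28 is a separate matter.

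**Assumptions.** The article gives no SD. LVEF is taken as normal and NT-proBNP as log-normal with a log-SD of 0.3 to 1.0. Pearson is read charitably as the chi-square goodness-of-fit test with equiprobable bins, fitted mean and SD, and bins − 3 degrees of freedom. Each arm is tested at 5%, and the t test is used only if both arms pass.

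**Step 1: chance diversion of normal data.** 1 − 0.95² = 0.0975, about 10%. Simulation with 11 bins agrees: 1 − 0.895 = 10.5%.

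**Step 2: how often both skewed arms pass as normal (63 per arm).**

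| Assumed log-SD | Both arms pass, 5 to 13 bins |
|---|---|
| 0.3 | about 57–60% |
| 0.5 | about 10–21% |
| 0.7 | about 0.4–3% |
| 1.0 | essentially never |

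The 5, 8 and 13-bin results at log-SD 0.5 are about 21%, 10–11% and 11–12%, so the bins alone can halve the rate. A separate run with 11 bins gave 56% at log-SD 0.3 and 9% at 0.5, the same picture within simulation error.

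**Step 3: does the choice of normality test matter?** Comparing the 11-bin Pearson test with Shapiro-Wilk, the two select different branches in 15% of trials with normal data, 48% at log-SD 0.3, 9% at 0.5 and none at 1.0.

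**Step 4: does the branch matter?** With a true difference of 0.5 SD (on the log scale for skewed data), the t test and the rank-based test disagree on significance in 5.5% of trials with normal data, 8% at log-SD 0.3 and 10% at 0.5.

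**Step 5: type I error.** The two-stage rule rejects in 4.8–5.3% of null trials, against 4.2–5.0% for a fixed t test and 4.6–5.2% for a fixed rank-based test (two-sided 5%).

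**Step 6: power.** For normal data with a 0.5 SD effect, power is 79.8% under the rule and 79.9% with a fixed t test. For NT-proBNP, the 58% and 32% falls are read as a geometric-mean ratio of 0.42/0.68 = 0.62. That reading is an assumption, because section 2.7 uses them as proportions. At log-SD 0.5, raw-scale and log-scale t tests both have 99.9% power. At log-SD 1.0 they have about 58% and 76%. Step 2 shows that such data go to the rank branch, where the rule has about 74%.

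**The case against.** The strongest defence is that section 2.11 does state a rule beforehand, and that the rule behaves acceptably: type I error is near 5% and little power is lost. That stands. The analysis is not a free choice made after seeing results, and the point should not be put that way. What remains is that the rule leaves its branch open until the data are in, and is too loosely specified for two analysts to be sure of taking the same branch.

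A second defence is that an unseen analysis plan may settle the details. But the article does more than omit detail: it states a selection rule and names a test for it. A plan that follows the article inherits the problem, and one that does not would contradict it.

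A reader might also infer more than the article supports:

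- **That the method is picked with knowledge of allocation.** Section 2.6 conceals allocation from staff analysing outcomes, and a pooled, blinded normality check would fit section 2.11.
- **That skewed NT-proBNP would be passed as normal in 33–45% of cases at log-SD 0.5.** That is the rate for one arm. Both arms must pass, and 0.45² = 0.20 and 0.33² = 0.11.
- **That the trial risks the drop in power seen on the raw scale at log-SD 1.0.** The binned test almost never passes data that skewed. Where it does pass skewed data, at log-SD 0.5, no power is lost.

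**Conclusion.** The point holds as one of specification. A poorly named, underspecified normality test is the only rule choosing the test and summary for NT-proBNP and LVEF, so their effect measures are not known in advance and may not match each other or agree across analysis sets. The diversion and pass rates in the working depend on the charitable reading of the test, on testing each arm at 5%, and on the assumed distributions. They show how unsettled the branch is; they are not estimates for this trial. There is no case for alpha inflation or a large power loss. The change is worth making because it is cheap and concerns the primary analysis, but the present rule does not make the trial invalid.

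**What to change.** In section 2.11, delete the normality test as the rule that selects the analysis. Name one analysis per primary and use it in both analysis sets:

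- **NT-proBNP:** natural log of the week-8 value, compared between arms by a linear model adjusted for the log baseline value, reported as a ratio of geometric means.
- **LVEF:** week-8 value in percentage points, compared by a linear model adjusted for baseline LVEF, reported as a difference in means.

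Check residuals after the fit, and give a rank-based two-group comparison as a sensitivity analysis only. Continuous secondary outcomes should likewise have their scale stated in advance.

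The cost is a few sentences. Both baseline values are already scheduled in Table 3, so no extra data or patients are needed. The one downside is that the NT-proBNP effect becomes a ratio instead of a difference in concentration. If a full protocol or analysis plan already fixes these analyses, the article's text should be brought into line with it.
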